### Randomization

Health centers with catchment HPs that provide POCT for ANC services will be listed and randomized to begin the intervention at T2 (i.e., the first randomized set of facilities) or T3 (i.e., the second randomized set of facilities). These facilities will be randomized 1:1 before T1 to two different intervention start times (i.e. two sequences), stratified by location and client volume, using randomly permuted blocks of size 2 and 4. We will use centralized randomization as the allocation concealment mechanism. A remote and independent statistician in the Johns Hopkins Bloomberg School of Public Health (JHSPH) will generate and implement the allocation sequence, and communicate it to the study sites after confirming the eligibility of the clusters. Health extension workers will identify pregnant women and provide the list of women to Addis Continental Institute of Public Health (ACIPH). ACIPH field workers will take consent and enroll eligible women.

**
*Blinding*:** Study staff and those assessing outcomes will not be blinded to knowing the study time period to which facility is randomized. The participants will also not be blinded about the type of care they will be receiving (G-ANC or routine/conventional care).

### Study implementation

Group ANC at the HP level is a new intervention, therefore the study will be rolled out using a phased approach.

**
*Pilot phase*:** Prior to study activation, we will pilot G-ANC in up to five purposively selected HPs in Amhara region that will not be included in the study. This pilot phase will allow us to adapt G-ANC materials to adjust for the literacy levels of the HEW and conditions at the HP. After the materials have been adapted, up to two HEWs per HP (total 10 HEWs) will be trained to facilitate G-ANC. In the pilot phase, we will enroll a maximum of 50 women (up to 10 per HP x up to 5 HPs). The pilot phase will determine feasibility, i.e., whether HEWs are able to facilitate the G-ANC meetings, there are enough eligible ANC clients at the HP level, we are able to enroll enough women at the HP who are of a similar gestational age, and women come back to the HP for the G-ANC meetings. After completing at least two G-ANC meetings in the pilot, we will determine the feasibility of moving to Phase 2 of the study. Training modules, data collection tools, and intervention delivery models will be refined, with the added engagement of midwives and health staff, based on pilot study feedback.

**
*Trial phase*:** Phase 2 includes T1, T2, and T3. During T1, pre-intervention data will be collected from the first set of 18 HPs by interviewing pregnant women during their pregnancy and again postpartum. The women in T1 will not receive the intervention. During T2, the G-ANC intervention will be implemented in the first set of 18 HPs (first six clusters), and pre-intervention data collection will be conducted in the second set of 18 HPs (i.e., second six clusters). During T3, the G-ANC intervention will be implemented in the second set of 18 HPs. If the first set of 18 HPs chooses to continue the G-ANC intervention with a second cohort, an additional six months of data collection will occur during T3. Participant timeline is depicted in
Figure 2.

**Figure 2. f2:**
[figure not shown]
G-ANC study timeline with pilot and trial phases.

Once study participants are enrolled, the participant timeline is about 8.5 months: enrollment with a baseline questionnaire, follow-up for about six months during ANC, and endline survey up to six weeks post-delivery. Participants in the qualitative research will have a single contact for the IDIs.

The overall duration of the entire study is 25.5 months. The implementation process will be documented in these sites, with some corrective measures expected to be taken after each block, depending on implementation process documentation, findings from pause and reflect sessions, and qualitative study findings before commencing the next block. A transition plan will also be developed by Jhpiego to hand over implementation to the government.

### Participant retention

Implementation of a paper-based participant tracking system will be used to accurately assess participant retention in the study. The G-ANC registration and participating registration book will be used to track ANC attendance. This will provide the HEWs with a listing of all participants who have missed scheduled G-ANC meetings.

### Data collection

Both quantitative and qualitative data collection approaches will be used in this study. Data will be collected in the pilot phase and then during study implementation (Phase 2).

Once enrollment begins, all new ANC attendees in the selected HPs will be screened for eligibility during the first ANC contact with a health care provider. The screening and enrollment questionnaire will be completed. Basic demographic data will be collected from all eligible consented women (all who meet the inclusion criteria). All data will be de-identified for those who decline study participation. Baseline and endline data will be collected from all eligible and voluntary women participating in all study time periods. During the first period, data will be collected from 18 control HPs. In the second period (T2), data will be collected from 18 intervention and 18 control HPs. In the third period, (T3) data will be collected from 18 intervention HPs.

Data quality will be monitored through the use of trained research assistants and supervisors, data quality supervision, and use of an electronic data collection program to minimize data entry errors.

The study team will select respondents for the IDIs at the end of the study based on preliminary findings from the quantitative survey. IDIs with women will be conducted at the end of T2 and T3, after completion of all G-ANC meetings (
Table 7). Specific topics/domains to explore with G-ANC participants include satisfaction with care, any perceived changes in self-efficacy or empowerment, health literacy, improved communication and/or trust with providers and the health system as a whole, factors in uptake/non-uptake of postpartum family planning, and the overall impression of the G-ANC model. In this study, we will use standardized pretested tools to assess the levels of empowerment, self-efficacy, and satisfaction. For empowerment and self-efficacy, we will use eight questions related to their current pregnancy and calculate a composite score to understand the woman's level of empowerment. We will ask 11 questions about their satisfaction with the ANC received during their last pregnancy and with the G-ANC for their current pregnancy.

**Table 7. T7:** Data collection timing, per tool.

Data collection tool	Study participant	Timing of data collection		
		T1	T2	T3*
Cluster level information	HP level information	18 HPs	36 HPs	18 HPs
Tool 1a. Screening and enrollment questionnaire	Pregnant women (ANC clients)	18 HPs (180 women) control	36 HPs (360 women) (intervention and control)	18 HPs (intervention) starting G-ANC
Tool 1b. Screening and enrollment log		18 HPs (180 women) control	36 HPs (360 (intervention and control)	18 HPs (intervention) starting G-ANC
Tool 2. Baseline client survey at ANC1		18 HPs (180 women) control	36 HPs (360 (intervention and control)	18 HPs (intervention) starting G-ANC
Tool 3. Endline client survey		18 HPs (180 women) control	36 HPs (360 (intervention and control)	18 HPs (intervention) starting G-ANC
Tool 4. G-ANC enrollment register	Pregnant women (ANC clients), intervention only	NA	180 women enrolled G-ANC	180 women enrolled G-ANC
Tool 5. IDI guide, ANC participants	Pregnant women (ANC clients), intervention and control HPs	NA	T2 endline (intervention site)	T3 endline (intervention site)
Tool 6. IDI guide, HEWs	HEWs, intervention and control HPs	NA	T2 endline (intervention site)	T3 endline (intervention site)
Tool 7. IDI guide, health facility managers	District managers, health facility managers, intervention and control HPs	NA	T2 endline (intervention site)	T3 endline (intervention site)

In-depth interviews will be conducted by experienced research assistants with a master’s degree in public health with HEWs trained in G-ANC and who facilitated G-ANC meetings in intervention sites and health managers. Specific topics/domains using open-ended guiding tools to explore with providers will include attitudes towards providing G-ANC; perceived changes in their communication and relationship with patients (if any); changes in empowerment, self-efficacy, and satisfaction related to their perceived ability to do their job well; changes in workloads; sustainability of group care; suggested changes to the model/logistics required to offer G-ANC; and perceived effects of G-ANC on colleagues and clients. IDIs with health facility managers and regional health managers will be conducted at the end of T2 and T3 in the intervention areas.

### Data analysis

**
*Quantitative data analysis.*
** Data analysis and the reporting of results for this study will be conducted in accordance with norms for analyzing cluster randomized trials as described in the Consolidated Standards of Reporting Trials guidelines with considerations for the step-wedge extension (
Hemming *et al.*, 2018;
Hemming *et al.*, 2019). If there is variation within the clusters, the statistical analysis will be adjusted based on the pollution levels. The primary analysis will be conducted using intention-to-treat analysis. After exploring balance by time period/intervention status and correlations, the effect of G-ANC will be estimated using generalized linear mixed effects models with binomial distribution and logit-link. The model will include G-ANC as the intervention indicator, time period and their interaction as the primary predictors, and HC as the random intercept. We will adjust for facility- and individual-level characteristics that show imbalance between the intervention vs. control time periods and can be strongly correlated with the outcome scores. The primary outcomes will be compared across time periods both within the intervention and control groups. Comparisons will be made within a given time period (e.g., T1, T2, and T3) for both the intervention and control conditions. The amount of missing data will be assessed for each variable and overall, for the sample. If more than 5% of data on covariates are missing, multiple imputation procedures will be used assuming data are missing at random (
Sterne *et al.*, 2009).

**
*Qualitative data analysis*.** Following each audio recording, either the moderator or an official transcriber familiar with local language and English will transcribe from the audio recording. Analysis will be thematic content analysis with similar themes and subthemes. Coding of textual passages will be done using open code 4.03 Umeå: Umeå University, an open-source tool known for qualitative analysis.

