### Intervention

During the intervention time period, pregnant women who come for their first ANC visit at the HP will receive standard individual care. At the end of this first ANC visit, eligible women who agree to participate in G-ANC will be added to the G-ANC cohort. Approximately eight to 10 women will be enrolled in a cohort. Cohort membership will be fixed (i.e., the same women and facilitators at each meeting). Two additional pregnant women who meet study criteria can be added to a G-ANC cohort if added to the cohort by the start of the second G-ANC meeting. Six monthly G-ANC meetings will be conducted for each cohort on a fixed day/time at each HP. Each cohort will meet for G-ANC meetings in a designated meeting space that is set up to ensure privacy during clinical consultations. The G-ANC meeting will be conducted by at least one HEW who is trained in the G-ANC service delivery model.

Each meeting will have the same general structure: self-assessment by the clients/peer-to-peer self-assessment initially taught and supervised by the HEW, such as measurement of weight and blood pressure using an automated cuff; individual assessments/clinical care by the HEW in a private space; discussions around pre-determined and appropriate gestational-age themes using illustrative cards and take-home booklets designed for G-ANC; and plan/reflect and peer-support activities that create group cohesion.
Table 2 presents the G-ANC meeting schedule and content per meeting. Each meeting is expected to last 90–120 minutes and will be documented as an ANC contact. Social distancing in response to COVID-19 as per national guidelines will be enforced during meetings. Women will have the opportunity for additional private time with the HEW after the G-ANC meeting if desired or needed for health and/or safety. Women will be told that they can and should return at any time if they have questions or concerns. Phone/text reminders will be used to remind participants of G-ANC meetings as a strategy to improve ANC attendance.

**Table 2. T2:** G-ANC intervention meeting schedule.

Meetings	Timing (gestational age)	Theme/Meeting Plan
Meeting 1	4–5 months	• Introduction to group care • Preventing problems in pregnancy • Teach self-assessments
Meeting 2	5–6 months	Danger signs during pregnancy • Sexually transmitted infection (STI) transmission and partner communication/negotiation

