Ministry of Health Ethiopia, 2022). Intervention materials in Amharic language include a pictorial self-assessment card women use at the beginning of each meeting to record weight, blood pressure, and any danger signs; meeting guide used by the facilitators to guide each meeting; five to six A4-size illustrated picture cards per meeting that are designed for nonliterate audiences (total 36 cards) and questions on the back of each card to foster discussion; an A4-sized booklet with small versions of all the picture cards that women can take home to share what they’ve learned with their partners and families; an implementation guide for HEWs to introduce G-ANC in their HP; a simple G-ANC register to aid the facilitator to track attendance and record other data; and three monitoring tools, including a meeting observation checklist to provide feedback and assess fidelity. The picture cards were pretested with HEWs before the pilot phase, and all the intervention materials will be revised as needed based on the pilot feedback. Each intervention HP will be provided with 12 chairs; a basic set of supplies and commodities, including POCT reagents to run activities; two weigh scales; three user-friendly Microlife PSA blood pressure devices for the self-assessments; and one privacy screen to divide the private clinical consultation area from the larger G-ANC meeting space.

All clients will continue to receive the components of standard care, and no standard therapies will be denied to the intervention group. Likewise, standard, individual ANC care will not be denied if requested at any time.

**
*Training*

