### Outcomes

**
*Primary outcome 1*:** Proportion of women with at least four ANC visits.

**
*Primary outcome 2*:** Proportion of women who delivered in a health facility.

After exploring the balance by time period/intervention status and correlations, the effect of G-ANC will be estimated using generalized linear mixed effects models with binomial distribution and logit-link.

We will adjust for facility- and individual-level characteristics that show imbalance between the intervention versus control time periods and can be strongly correlated with the outcome scores. The primary analysis will not adjust for multiplicity and will be performed at 0.05 level of statistical significance.

**
*Secondary outcomes*:** Satisfaction level of women with ANC services, proportion of women who reported self-efficacy or empowerment.

Analysis of secondary outcome measures will follow a plan similar to the analysis of the primary outcome. Subgroup analysis will be conducted for specific subgroups to determine if the interventions were different. The key subgroups of interest are marital status, education, and economic status.

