**Table 6. T6:** Summary of sample size for qualitative data collection.

Study population	Estimated number of IDIs per round of data collection (after pilot, after T2 and after T3)	Total
Women who completed most G-ANC meetings	Up to 9, in 3 rounds	27
Women who dropped out of G-ANC after 1–2 meetings	Up to 9, in 3 rounds	27
Women who completed most G-ANC meetings, but did not give birth in a health facility	Up to 9, in 3 rounds	27
Women who completed most G-ANC meetings and gave birth in a health facility	Up to 9, in 3 rounds	27
HEWs	Up to 5, in 3 rounds	15
Health facility managers	Up to 1 per facility, 18 HPs T2 and 18 HPs T3	36
District/Regional managers	Up to 1 per woreda manager Up to 1 per regional manager	15 3

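### The Data analysis section adjusts the analysis for undefined 'pollution levels' without keeping that adjustment out of the intention-to-treat primary analysis

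*Protocol article*

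**What the plan says.** The quantitative part of Data analysis gives a conditional rule: "If there is variation within the clusters, the statistical analysis will be adjusted based on the pollution levels". The sentence that follows is "The primary analysis will be conducted using intention-to-treat analysis". The model is then specified: "The model will include G-ANC as the intervention indicator, time period and their interaction as the primary predictors, and HC as the random intercept". A separate sentence allows adjustment for facility and individual characteristics that are imbalanced and related to the outcome. Contamination is not mentioned there, nor in the Outcomes section, which names the same model family.

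Four other statements bear on the point:

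- **Outcome.** Primary outcome 1 is "Proportion of women with at least four ANC visits" (Outcomes).
- **Exposure.** Each G-ANC meeting "will be documented as an ANC contact" (Intervention).
- **Movement between forms of care.** "Likewise, standard, individual ANC care will not be denied if requested at any time" (Intervention). Table 6 also plans interviews with a group described as "Women who dropped out of G-ANC after 1–2 meetings".
- **Timing.** "These facilities will be randomized 1:1 before T1 to two different intervention start times" (Randomization).

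**The concern.** Intention-to-treat compares women by the condition assigned to their cluster and period, whatever care they went on to receive. A rule that adjusts the analysis for contamination, once some within-cluster variation is seen, brings received care back in. The two can coexist only if the adjusted analysis is kept apart from the primary one, and the article does not do that.

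The matter is sharper here than in most trials because exposure to G-ANC is partly the outcome: every meeting attended adds to the visit count. Women who stay in group care are also likely to be women who seek care anyway. Adjusting on exposure can therefore produce a difference in four or more visits when the intervention has no effect.

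The rule is also triggered by the data. Staff and outcome assessors are not blinded (Randomization), and the T1 and T2 surveys had been completed by September 2024 (Study status), so an adjustment of unspecified form could be chosen with results in view.

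**Working it through.** **1. The passages side by side.** The adjustment sentence governs the statistical analysis in general, says that it will be adjusted, and carries no label such as secondary or sensitivity. The next sentence says that the primary analysis is intention-to-treat. The listed model has four elements (G-ANC indicator, period, their interaction, health-center random intercept) and none is a pollution term. A reader cannot tell from the text whether the primary analysis includes the adjustment.

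**2. When contamination would be observed.** Health centers are randomised before T1. Receipt of G-ANC by controls, or departure from G-ANC by intervention women, can only happen later, so on this reading the adjustment variable is post-randomisation.

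**3. Link to primary outcome 1.** A woman who has her first individual visit and then leaves after one or two meetings has 1 + 1 = 2 or 1 + 2 = 3 contacts from the programme. She reaches four only through further individual visits, which remain open to her.

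**4. The plan's own figure.** The Sample size section gives 84% power for an odds ratio of 2 with 12 health centers, three periods, 30 women per center-period and ICC 0.10.

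- Target proportion: odds 2 × 0.315/0.685 = 0.920, so 0.479. Planned difference: 0.479 − 0.315 = 0.164.
- Total variance 0.315 × 0.685 = 0.2158, so τ² = 0.0216 and s² = 0.9 × 0.2158/30 = 0.00647.
- Hussey-Hughes design sums with I = 12, T = 3: U = 18, W = 180, V = 30.
- Variance = I·s²(s² + Tτ²) / [(IU − W)s² + (U² + ITU − TW − IV)τ²] = 0.00553 / (36 × 0.00647 + 72 × 0.0216) = 0.00310, so SE = 0.0556.
- Power = Φ(0.164/0.0556 − 1.96) = Φ(0.99) ≈ 83.9%, two-sided 0.05 assumed.

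The figure is reproduced for the complete design (83.1% for facility delivery). It does not bear on the contradiction, but it supplies the 0.164 yardstick used below.

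**5. Null simulation for outcome 1.** The true effect was zero, with 600 runs per scenario.

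- From the document: the Table 5 layout (6, 12 and 6 health centers in T1, T2 and T3, 30 women each), base rate 0.315, ICC 0.10.
- Assumed: drop-out from group care of 10%, 20% or 30%; control crossover of 0%, or 10% alongside 20% drop-out; and a standard normal care-seeking trait f.
- Outcome: logit P(Y = 1) = b₀ + u(center) + γf. Receipt of G-ANC: logit P(A = 1) = k + γf, with k set to the assumed drop-out or crossover. γ = 0, 0.75 or 1.5 (no, moderate or strong link).
- Fitted model: linear mixed model with period effects and a health-center random intercept. It stands in for the planned logit model and omits the interaction.

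Mean estimated risk difference (truth 0):

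| Analysis | Moderate link, drop-out 10/20/30% | Strong link, drop-out 10/20/30% | 20% drop-out + 10% crossover, moderate/strong |
|---|---|---|---|
| Intention-to-treat | −0.001 / 0.000 / 0.000 | 0.000 / +0.003 / −0.002 | −0.007 / +0.002 |
| Woman-level covariate | +0.008 / +0.018 / +0.027 | +0.023 / +0.050 / +0.068 | −0.004 / +0.006 |
| Center-period share as covariate | +0.008 / +0.020 / +0.039 | +0.025 / +0.042 / +0.066 | −0.004 / +0.007 |
| Excluding affected women | +0.009 / +0.018 / +0.028 | +0.023 / +0.050 / +0.069 | +0.021 / +0.078 |
| Regrouping by care received | +0.049 / +0.067 / +0.076 | +0.120 / +0.170 / +0.193 | +0.082 / +0.220 |

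With no link (γ = 0), every analysis lay between −0.007 and +0.004.

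Rejection at nominal 5% was 6% to 8% for intention-to-treat in all scenarios, which reflects a normal critical value with 12 clusters. With one-sided drop-out, the covariate versions rejected in 5% to 9% of runs (moderate link) and 7% to 18% (strong link). Regrouping rejected in 14% to 38% and 58% to 99%.

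**The case against.** The strongest reply is that the meaning is inferred. The article never defines pollution and never uses the word contamination. It could be a slip for another word, such as population: the article has other slips, health posts serve populations of a stated size, and client volume is a stratifier. Adjustment for a baseline population characteristic is compatible with intention-to-treat, and the bias argument would then fall away. This stands, and it is why the point is conditional. It does not rescue the sentence, which would still make a covariate depend on variation seen in the data.

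Second, the next sentence and the listed model can be read as settling the primary analysis. That is a fair way to read the authors' intention, but the rule that precedes them is worded without exception.

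Third, an article may leave the definition and form of an adjustment to the full protocol or SAP. Agreed, and their absence is not the complaint. The complaint is a stated rule that conflicts, as written, with the declared primary analysis.

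A reader might go further and infer that early leavers will be excluded or counted as unexposed. With proportion p and leaving fraction d, that would compare p/(1 − d) with p or p/(1 + d), and for assumed d of 5% to 20% it yields apparent odds ratios from 1.08 to 2.33 under no effect (the highest at an assumed 50% base rate). The documents do not support presenting these as the consequence of the sentence. It says adjusted, not excluded or moved. Table 6 is a sampling category for interviews, not a drop-out rate. The calculation also needs every early leaver to miss four visits, although individual ANC stays available. Contamination in its usual sense, controls receiving G-ANC, also has limited opportunity, since T2 controls belong to different health centers and cohorts are fixed.

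**Conclusion.** The point holds in a limited form. The article states a data-triggered adjustment, does not confine it to a secondary analysis, and then declares an intention-to-treat primary analysis whose model has no place for it. If pollution means contamination, carrying out the adjustment in the primary analysis would condition on a post-randomisation quantity tied to four or more visits, and it could bias the result.

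The size is not fixed by the document. Under assumed one-sided drop-out of 10% to 30% with a moderate or strong link to care-seeking, covariate adjustment gave about +0.01 to +0.07 on the risk scale. Regrouping by care received gave +0.05 to +0.19, against a planned 0.164. With 10% control crossover added, the covariate versions were within 0.01 of zero. With no link there was no bias. The drop-out rates, the crossover rate and the strength of the link are all assumptions. A reader might infer that the bias must favour G-ANC. That is the direction in the one-sided scenarios tried, but it is not established in general. The stated power and sample size are unaffected.

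**What to change.** Remove the sentence from the primary analysis. State that all women are analysed by the condition assigned to their health center in the period in which they enrolled, whatever G-ANC exposure they had. Report contamination descriptively, and place any contamination-adjusted analysis in a labelled sensitivity analysis.

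If another word was intended, such as a baseline population characteristic, correct the word and fix that covariate in advance instead of letting its use depend on observed variation.

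The cost is a sentence or two of wording, with no change to sample size or data collection. The one downside is that the intention-to-treat estimate may be slightly diluted if contamination occurs. The change should be made and dated before any further outcome analysis: T3 was still pending when the article reported its status in September 2024.

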### Study status

The study as of September 2024, the study i active. Quantitative baseline and endline surveys of T1 and T2 have been conducted. Currently, preparations are underway for T3, but implementation of this step may be delayed until security improves in the region.

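### With three-level time period, the primary model's G-ANC by period interaction cannot be estimated, because T1 has no G-ANC and T3 has no control; only the T2 effect is identified.

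*Protocol article*

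**What the plan says.** The Data analysis section names "generalized linear mixed effects models with binomial distribution and logit-link" and then lists the terms: "The model will include G-ANC as the intervention indicator, time period and their interaction as the primary predictors", "and HC as the random intercept". It adds: "Comparisons will be made within a given time period (e.g., T1, T2, and T3) for both the intervention and control conditions". It does not say which coefficient or contrast is to be reported as the effect of G-ANC.

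The data layout comes from Data collection and Study implementation:

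- T1: "During the first period, data will be collected from 18 control HPs", and "The women in T1 will not receive the intervention".
- T2: "In the second period (T2), data will be collected from 18 intervention and 18 control HPs".
- T3: data come from the 18 health posts of the second set, all on G-ANC. The first set may choose to run a second G-ANC cohort in T3. That option adds G-ANC women and no controls.

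**The concern.** An interaction between condition and period asks for a separate G-ANC effect in different periods. That needs both conditions in more than one period, and here only T2 has both. The model as written therefore asks for effects on which the trial collects no information. The article names no contrast, so the software's handling of redundant terms would settle what the G-ANC coefficient means.

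This matters because one possible meaning is a comparison across time. The abstract says that ANC attendance and facility births are rising in Ethiopia. Study implementation allows corrective changes between blocks, and Study status reports that for T3 "implementation of this step may be delayed until security improves in the region". None of this affects whether the model can be estimated. It does mean that a T3-against-T1 contrast could not be read as the effect of G-ANC.

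The sentence on comparisons within T1, T2 and T3 raises the same problem if it means intervention against control.

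**Working it through.** **1. The model that matches the stated power.** The Sample size section gives 84% power for an odds ratio of 2 with 12 HCs, three periods, 30 women per HC and period, and ICC 0.10. I used the Hussey-Hughes variance for a stepped wedge with categorical period, one common G-ANC effect and no interaction:

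Var = Iσ²(σ² + Tτ²) / [(IU − W)σ² + (U² + ITU − TW − IV)τ²]

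Here I = 12 and T = 3. In the complete design with six HCs per sequence:

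- U = 6×2 + 6×1 = 18
- W = 0² + 6² + 12² = 180
- V = 6×2² + 6×1² = 30
- IU − W = 216 − 180 = 36
- U² + ITU − TW − IV = 324 + 648 − 540 − 360 = 72

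Four or more ANC contacts, with variance taken at the control proportion:

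- Total variance 0.315×0.685 = 0.2158; τ² = 0.02158; σ² = 0.1942/30 = 0.00647.
- Var = 12×0.00647×0.0712 / (36×0.00647 + 72×0.02158) = 0.00310, so SE = 0.0556.
- The odds ratio of 2 gives 0.63/1.315 = 0.479, a difference of 0.164.
- z = 2.95, and with two-sided 0.05 (sidedness is not stated) power = Φ(2.95 − 1.96) = 83.9%.

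The same steps for facility delivery (0.271 to 0.426) give 83.1%. The stated 84% is thus reproduced by a model without the interaction. Other variance conventions and logit-scale versions give 73–81%.

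**2. Rank of the model as written.** Let G indicate G-ANC, with T1 as the reference period.

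| Cell | 1 | T2 | T3 | G | G×T2 | G×T3 |
|---|---|---|---|---|---|---|
| T1 control | 1 | 0 | 0 | 0 | 0 | 0 |
| T2 control | 1 | 1 | 0 | 0 | 0 | 0 |
| T2 G-ANC | 1 | 1 | 0 | 1 | 1 | 0 |
| T3 G-ANC | 1 | 0 | 1 | 1 | 0 | 1 |

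There are six columns and four distinct, independent rows, so the rank is 4. The two dependencies are T3 = G×T3 and G = G×T2 + G×T3. The optional first-set cohort repeats the last row, and a complete stepped wedge has these same four rows, so the rank is 4 in all three layouts. The random intercept for HC does not change this. The model without the interaction (1, T2, T3, G) already has rank 4, so the interaction adds no information.

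**3. What is identified.** Write the cell logits as a; a + t2; a + t2 + g + gt2; a + t3 + g + gt3. The difference between the two T2 cells gives g + gt2, the T2 effect. With no control in T3, t3 and g + gt3 appear only as a sum. Not identified: g, gt2, gt3, the T3 effect g + gt3, and the average of the T2 and T3 effects.

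**4. What the G coefficient becomes.** Removing two redundant columns gives five full-rank choices:

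- Drop G×T2 and G×T3: G is T2 G-ANC against T2 control.
- Drop T3 and G×T2: the same T2 contrast.
- Drop T3 and G×T3: G is T3 G-ANC against T1 control.
- Two further choices drop G itself.

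To illustrate the third choice, take a true odds ratio of 2 and an assumed secular trend per period on the logit scale. The trends are assumptions, not figures from the article.

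| Trend per period | T2 contrast | T3 G-ANC vs T1 control |
|---|---|---|
| 0 | 2.0 | 2.0 |
| 0.2 | 2.0 | 2×exp(0.4) = 2.98 |
| 0.4 | 2.0 | 2×exp(0.8) = 4.45 |

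**5. After removing the interaction.** In the 720-woman layout, generalised least squares gives weights of +1 on T2 G-ANC, −1 on T2 control and 0 on T1 and T3. The odds ratio then rests on the concurrent T2 comparison of 6 against 6 HCs. If all six first-set HCs also supply a T3 cohort of 30 women, T3 enters with weights −0.77 (first set) and +0.77 (second set). This weight is 0.1/(0.1 + 0.9/30) = 0.769, the correlation between an HC's means in two periods.

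**The case against.** Several counter-arguments have force.

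*The T2 effect survives.* The sum g + gt2 is the same whichever redundant columns are dropped, and software that enters main effects first will usually print that contrast as G. This stands. A reader might infer that the trial has no defined primary effect at all, but the design does not support that: a randomised T2 effect exists and can be estimated. The fault is an over-specified model with no contrast named.

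*Period could be linear.* With one linear time term the model has four columns and rank 4. The article does not say that period is categorical, so the finding is conditional on that. Three labelled periods make a factor the natural reading. With linear time, the G coefficient would be the effect at whatever time is coded zero, and the interaction would rest on straight-line extrapolation.

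*Period is in the model.* A reader might infer that analysts are free to leave period out, turning the analysis into a before-after comparison with apparent power above 99%. The Data analysis section lists time period as a primary predictor, so that choice is not left open.

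*The within-period sentence is loose.* It may mean only that results will be shown by period. The objection to it therefore applies only if it means intervention against control.

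*The optional cohort.* It would be wrong to say without qualification that the corrected odds ratio is a T2-only estimate, since T3 contributes if the first set's second cohort is collected and analysed. This stands and is reflected in the fix.

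**Conclusion.** The point holds: with time period as a three-level factor, the primary model in the Data analysis section cannot be estimated as written. Six fixed-effect columns have rank 4 in the 720-woman layout, with the optional T3 continuation, and in a complete stepped wedge, so more data of the planned kind would not cure it. This is a stated rule that does not fit the design, rather than detail left to an analysis plan.

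The size of the consequence depends on which terms are dropped. Two of the three choices that keep G return the randomised T2 contrast; the third returns a contrast confounded with time. The odds ratios of 2.98 and 4.45 rest on assumed trends and show only how far that third choice could drift.

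An intervention-against-control comparison within a period is possible only at T2. The T1-to-T2 and T2-to-T3 contrasts are before-after comparisons. The article does not call them primary, so their bias does not carry into a period-adjusted primary effect.

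A reader might also want to fold in the gap between the 84% power, calculated for the complete design, and the 720-woman layout. That gap comes from the data layout and not from the interaction. It is a separate issue, and this point does not need it.

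**What to change.** In the Data analysis section:

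1. Delete the interaction. State the primary model as categorical period (three levels), G-ANC and the random cluster term, with one G-ANC odds ratio as the reported effect.
2. State that in the 720-woman layout this odds ratio rests on the concurrent T2 comparison of 6 against 6 HCs, and that T3 also contributes if the optional first-set T3 cohort is collected and analysed. Say in advance whether that cohort will enter the primary analysis.
3. Limit intervention-against-control comparison within a period to T2.
4. Label the T1-to-T2 and T2-to-T3 contrasts descriptive and not adjusted for time.

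The cost is a few sentences, with no change to conduct or data collection. The corrected model is also the one that reproduces the stated 84% power. The separate period-specific effects that the interaction seems to promise are given up, but the design could not supply them. Study status reports that the T1 and T2 surveys are done and T3 is in preparation, so the change can still precede the final analysis. It should be dated and recorded as made after T1 and T2 data collection.
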